## Abstract

**Background:**

The incidence of type 2 diabetes, cardiovascular diseases, and obesity has been rising dramatically; however, their pathogenesis is particularly intriguing. Recently, dysbiosis of the intestinal microbiota has emerged as a new candidate that may be linked to metabolic diseases. We hypothesize that selective modulation of the intestinal microbiota by probiotic or synbiotic supplementation may improve metabolic dysfunction and prevent diabetes in prediabetics. In this study, a synthesis and study of synbiotics will be carried out for the first time in Iran.

**Methods/Design:**

In a randomized triple-blind controlled clinical trial, 120 adults with impaired glucose tolerance based on the inclusion criteria will be selected by a simple random sampling method and will be randomly allocated to 6 months of 6 g/d probiotic, synbiotic or placebo. The fecal abundance of bacteria, blood pressure, height, weight, and waist and hip circumferences will be measured at baseline and following treatment. Also, plasma lipid profiles, HbA1C, fasting plasma glucose, and insulin levels, will be measured and insulin resistance (HOMA-IR) and beta-cell function (HOMA-B) will be calculated at baseline and will be repeated at months 3, 6, 12, and 18. The data will be compared within and between groups using statistical methods.

**Discussion:**

The results of this trial could contribute to the evidence-based clinical guidelines that address gut microbiota manipulation to maximize health benefits in prevention and management of metabolic syndrome in prediabetes.

**Trial registration:**

Iranian Registry of Clinical Trials: IRCT201511032321N2. Registered on 27 February 2016.

**Electronic supplementary material:**

The online version of this article (doi:10.1186/s13063-017-1885-8) contains supplementary material, which is available to authorized users.

## Background

Diabetes mellitus (DM), prediabetes, obesity, and cardiovascular disorders (CVD) are important public health problems in that their prevalence and incidence have been rising dramatically during the last decades [1]. The prevalence of prediabetes in the world exceeds 25% who are at higher risk of developing type 2 diabetes (T2DM), compared with individuals with normal glucose tolerance [2].

In addition to well-established risk factors for T2DM and CVD, including genetic predisposition and unhealthy lifestyle, an altered configuration of the microbial community in the gut has emerged as a new candidate that may be linked to these metabolic disorders [2, 3]. Studies suggest that aspects of the modern Western lifestyle, including high-fat diets and antibiotics, can alter commensal microbial communities. However, a full list of factors which are capable of altering gut microbiota remains incomplete [4]. Studies have shown that early intervention in patients with impaired glucose tolerance can significantly prevent type 2 diabetes [3]. Recent researches suggest that intestinal microbiota (i.e., Bacteria, Archaea and Eukarya residing in the gastrointestinal tract) are associated with low-grade chronic inflammation and may play a role in the pathogenesis of obesity- and cardiovascular disease -related events [5, 6]. The role of gut microbiota in metabolic disorders may be through influence on host nutrition and energy, intestinal epithelial homeostasis, and host immune system [7]. It is shown that endotoxin concentrations are higher in adults at risk of T2DM compared with normoglycemic individuals and are associated with an increased risk of insulin resistance, CVD, and incidence of type 2 diabetes [8, 9].

The distal gut microbiota is composed of billions of bacteria, of which Bacteroidetes and Firmicutes are the two dominant phylogenetic types [10]. Firmicutes are the largest phylum of bacteria, comprising more than 200 genera, and the Bacteroidetes include over 20 bacterial genera [11]. Most of the studies in humans and in mice have reported that obesity and impaired glucose metabolism are associated with an altered ratio of Firmicutes and Bacteroidetes [12, 13].

It is documented that the ratio of Bacteroidetes to Firmicutes is positively and significantly correlated with plasma glucose concentrations [8, 14]. In a study in mice, obesity has been associated with a 50% reduction in Bacteroidetes and increase in Firmicutes [15].

An approach for modulation in the gut microbiota is the use of oral viable strains of bacteria (probiotics), indigestible carbohydrates (prebiotics), or synergistic combinations of a probiotic and prebiotic (synbiotic) [16, 17].

Based on previous studies, prebiotics result in specific changes in the activity and/or composition of the gut microbiota mostly in rodent models, which can be beneficial for local and systemic host health. Most health aspects of prebiotics have been directed toward obesity and inflammation [18]. Furthermore, probiotic supplementation has been shown to reduce metabolic endotoxemia and improve glycemic control in rodents [19]. Therefore, it is hypothesized that prebiotic and/or probiotic supplementation may be a useful strategy to improve metabolic health, insulin resistance, and prevent type 2 diabetes, which could be interesting in the management of metabolic disorders in prediabetics. To establish the causality, well-designed and well-powered prospective studies in which an altered microbiome is documented during supplementation with probiotic, prebiotic or synbiotic are needed [20]. In this field, the evidence is limited and the results are inconsistent. The discrepancies between studies can be explained by ethnic or dietary differences. Also, knowledge on the long-term efficacy of these treatments and comparison of their effects in a randomized clinical trial is still lacking, especially in the human. The intervention period of most of the previous trials has been too short (less than 3 months) to observe the effects of these supplements. In addition, there are limited studies which explored the effects of probiotic or synbiotic administration in prediabetic individuals. Up to now, there has been no clinical trial to assess the effects of these supplements on insulin resistance and risk of diabetes development in patients with prediabetes.

Hence, this study has been designed to investigate the efficacy of probiotic and synbiotic administration in the development of type 2 diabetes and metabolic variables in prediabetics via a parallel-group randomized triple-blind placebo-controlled clinical trial.

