## The aims and hypotheses

### General aim

The general aim of the present investigation is to determine the effects of 6 months ingestion of probiotic or synbiotic on metabolic syndrome indices and gut microbiota composition through a triple-blind, randomized, placebo-controlled clinical trial in adults at risk of type 2 diabetes (prediabetes).

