### The specific aims and hypotheses

#### Aim 1

To determine whether probiotic or synbiotic supplementation improves fasting plasma glucose, insulin resistance (primary outcome), and beta-cell function in individuals at elevated risk of developing T2DM. We hypothesize that probiotic and synbiotic supplementation will improve fasting plasma glucose, insulin sensitivity, and beta-cell function in these individuals compared with placebo.

#### Aim 2

To determine whether probiotic or synbiotic supplementation will improve lipid profiles in individuals at elevated risk of developing T2DM. We hypothesize that probiotic and synbiotic supplementation will reduce serum triglyceride and non-high-density lipoprotein (HDL) cholesterol, elevate HDL cholesterol, and improve low-density lipoprotein (LDL)/HDL, total cholesterol (TC)/HDL and triglyceride (TG)/HDL in these individuals.

#### Aim 3

To determine whether probiotic or synbiotic supplementation will improve anthropometric indicators in individuals at elevated risk of developing T2DM. We hypothesize that probiotic and synbiotic supplementation will improve body mass index (BMI), waist circumference and waist-to-hip ratio (WHR) in these individuals.

#### Aim 4

To determine the changes in abundance and ratio of two dominant groups of gut microbiota including Firmicutes and Bacteroidetes and their relation with metabolic syndrome indices during supplementation. We hypothesize that the change in Gram-positive gut microbiota (Firmicutes) and Firmicutes-to-Bacteroidetes ratio with probiotic and synbiotic supplementation will be correlated with the change observed in the metabolic variables.

#### Aim 5

To compare the effects of probiotic and synbiotic supplements on gut microbiota, anthropometric, glycemic, and lipid profiles. We hypothesize that synbiotic supplements will have more efficacy to improve these indicators than probiotic.

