Inclusion criteria:	
Population: men and women 35–75 years old	
Prediabetic [FBG = 100–125 OR 2hBS = 140–199 (via OGTT)]	
Informed consent	
Exclusion criteria:	
Current smokers, suspected or definite history of alcohol or drug abuse history	
Antibiotic use in the past 3 months or during the treatment period	
Using probiotic, prebiotic or symbiotic during the past 3 months	
Noncompliance in consumption of the supplements	
Being pregnant	
Having gastrointestinal diseases, i.e., food allergies, celiac, irritable bowel disease,	
severe liver, kidney, heart, nervous system diseases	
Allergy to studied agents	
Currently taking prescribed nonsteroidal anti-inflammatory drugs, antipsychotics, nicotinic acid	

*FBG* fasting blood glucose, *2hBS* 2-hour blood sugar, *OGTT* oral glucose tolerance test

If a participant will be found to have missed >10% of supplement dose at follow-up, he or she will be excluded from the study. Also, the participants will be excluded from the study if there is any change in medication, they start antibiotics, or modify their lifestyle. The framework of the study has been provided in Fig. 1. Study visits will be scheduled for weeks 1, 2, 3, 5, 7, 9, 12, 14, 16, 18, 20, 24, 48, and 72. A table of the time schedule of enrollment, interventions, assessments, and visits for participants is provided in Table 2, and an overview of the timeline of the study interventions and assessments is provided in Fig. 2.

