### Biochemical assays

Participants who have met the inclusion criteria (Table 1) will be instructed to arrive at Isfahan Endocrine and Metabolism Research Center for laboratory testing between 7:00 and 9:00 am after a 12-hour overnight fast and not to do vigorous physical activity for the previous 48 hours. Each participant will be tested for the biochemical parameters at baseline and during each follow-up visit (3, 6, 12, and 18 months).

An oral glucose tolerance test (OGTT) will be performed to clarify glycemic status. Plasma lipid and lipoprotein concentrations (i.e., total cholesterol, high- and low-density lipoprotein cholesterol, and triglycerides) will be measured using a photometric assay kit (Pars Azmoon Co., Tehran, Iran). Fasting glucose levels will be measured using the glucose oxidase (GOD) method. Fasting insulin levels will be measured using chemiluminescence (Siemens, Munich, Germany). Ion exchange chromatography will be used to test glycosylated hemoglobin (HbA1c).

The homeostatic model assessment of insulin resistance (HOMA-IR) and homeostatic model assessment of beta-cell function (HOMA-B) index will be used to determine insulin resistance (primary outcome) and beta-cell function respectively using the following formula:$$ \mathrm{HOMA}\hbox{-} \mathrm{I}\mathrm{R}=\mathrm{fasting}\;\mathrm{blood}\;\mathrm{glucose}\;\left(\mathrm{mmol}/\mathrm{ml}\right)\times \mathrm{insulin}\;\mathrm{assay}\;\left(\mathrm{microunit}/\mathrm{ml}\right)/22.5 $$
$$ \upbeta \kern0.5em \mathrm{cell}\kern0.5em \mathrm{function}\kern0.5em \left(\mathrm{HOMA}\hbox{-} \mathrm{B}\right)=\left[\mathrm{fasting}\ \mathrm{insulin} \times 20\right]/\left[\mathrm{fasting}\ \mathrm{glucose}\hbox{-} 3.5\right] $$

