## Discussion

Up to now, the therapeutic effects of gut microbiota manipulation, through the administration of probiotics/prebiotics/synbiotics, have been discussed, but there is little information regarding if they improve metabolic indicators in humans. In addition, the potential benefits of these biopharmaceuticals in prediabetic individuals who are at high risk for developing type 2 diabetes and experiencing cardiovascular events has received little attention. This trial will address this important research gap, by exploring and comparing the role of probiotics and synbiotics in modifying anthropometric, glycemic, and lipid profiles among prediabetic individuals.

The innovative aspects of this clinical trial include: (1) testing hypotheses involving a novel concept for which there are little strong data in humans; (2) focusing on individuals at high risk for T2DM, including those with prediabetes; (3) carrying out a synthesis and study of synbiotics for the first time in Iran; (4) following up the participants for 1 year after the intervention phase; and (5) comparing the effects of probiotics and synbiotics.

Importantly, our findings could have a significant impact on clinical practice and public health as a simple and efficacious adjunctive approach for prevention or management of T2DM if our hypotheses are supported. The primary challenge of our study will be participant adhesion and retention. This challenge will be managed by the project coordinator who will have weekly contact with participants in which any concerns or issues will be immediately addressed.

If these supplements are shown to be effective in management of prediabetes and preventing diabetes, they would be a very attractive alternative or adjunctive for current medications.

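### Development of type 2 diabetes is a stated purpose that no aim, outcome or analysis takes up, and the exclusion for medication change conflicts with intention-to-treat

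*Protocol article*

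**What the plan says.** The Background closes by saying that the trial is meant to "investigate the efficacy of probiotic and synbiotic administration in the development of type 2 diabetes and metabolic variables in prediabetics". Development of diabetes and metabolic variables are named there as two separate things. The Abstract hypothesizes that supplementation may prevent diabetes, and the Discussion looks ahead to a conclusion on it: "If these supplements are shown to be effective in management of prediabetes and preventing diabetes".

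The formal objectives are narrower. The general aim is to "determine the effects of 6 months ingestion of probiotic or synbiotic on metabolic syndrome indices and gut microbiota composition". Aim 1 asks whether supplementation "improves fasting plasma glucose, insulin resistance (primary outcome), and beta-cell function in individuals at elevated risk of developing T2DM". Aims 2 to 5 cover lipids, anthropometry, gut microbiota and the comparison of the two active products. The sample size is for a standardized mean difference, and the main analysis is a repeated measures ANOVA.

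On data, participants are "tested for the biochemical parameters at baseline and during each follow-up visit (3, 6, 12, and 18 months". On the glucose tolerance test the article says only: "An oral glucose tolerance test (OGTT) will be performed to clarify glycemic status". Entry in Table 1 requires "Prediabetic [FBG = 100–125 OR 2hBS = 140–199 (via OGTT".

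On retention, the Overview states: "Also, the participants will be excluded from the study if there is any change in medication". The Sample size section says that outcome data will be gathered in full, including from people who stop or depart from the intervention. Treatment of missing data makes intention-to-treat the primary approach, with per protocol secondary.

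**The concern.** Two faults meet here. First, a purpose stated in the Background has no outcome, case definition or comparison behind it. A prevention statement in the final report would then have to rest on HOMA-IR and other continuous measures, or on a definition of diabetes chosen once the data are known.

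Second, the exclusion for medication change bears on exactly this question. A participant who progresses and starts glucose-lowering treatment has a change in medication. Excluding that person from the study makes the loss depend on the outcome. It would also take the person out of the primary analysis, which is declared to be intention-to-treat.

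**Working it through.** **1. Is the purpose carried forward?**

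| Place in the article | Onset of diabetes |
|---|---|
| Abstract (Background) | hypothesized benefit |
| Background, closing paragraph | stated purpose |
| General aim | not named |
| Aims 1–5 | not named as an outcome |
| Sample size | not used; standardized mean difference of 0.60 |
| Statistical analysis | not named; repeated measures ANOVA on the main outcomes |
| Discussion | anticipated conclusion |

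**2. What happens to a participant whose medication changes?** Under the Overview the person is excluded from the study. Under Sample size the outcome data are still collected. Under Treatment of missing data the person belongs in the primary analysis. The three cannot all be followed. Progression seen only on laboratory values, with no change in medication, would not trigger this exclusion.

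**3. Are the data there?** The Abstract and Biochemical assays schedule fasting glucose and HbA1c at baseline and months 3, 6, 12 and 18. The glucose tolerance test has no timing of its own and is not in the Abstract's list of repeated measures, so it cannot be assumed at follow-up.

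**4. Who would be at risk?** Table 1 joins its two glucose ranges with OR, so a person can enter on one value while the other lies above its ceiling. Table 1 has no HbA1c criterion. A baseline screen on all three measures is therefore needed before anyone is counted as a new case.

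**5. How precise would a comparison be?** The plan has no figure for this. Input from Sample size: n = 40 per arm. Assumptions, since the document gives no incidence: placebo risk p over follow-up of 10–30%, halved to q = p/2 on active treatment; two-sided alpha 0.05.

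Half-width of the 95% CI for the risk difference = 1.96 × √[p(1−p)/40 + q(1−q)/40].

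- p = 0.10: 1.96 × √(0.00225 + 0.00119) = 0.115
- p = 0.30: 1.96 × √(0.00525 + 0.00319) = 0.180

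Fisher power is the sum of the binomial probabilities of all 40-versus-40 tables with p ≤ 0.05. The normal approximation is shown beside it, with the number per arm it would need for 80% power.

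| Placebo risk | Expected events, placebo / active | Risk difference (points) | CI half-width (points) | Power, Fisher | Power, normal | n per arm for 80% |
|---|---|---|---|---|---|---|
| 10% | 4 / 2 | 5 | 11.5 | 4.3% | 13.2% | 435 |
| 15% | 6 / 3 | 7.5 | 13.8 | 10.0% | 18.3% | 278 |
| 20% | 8 / 4 | 10 | 15.5 | 16.2% | 23.7% | 199 |
| 30% | 12 / 6 | 15 | 18.0 | 28.1% | 36.0% | 121 |

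In every row the half-width exceeds the assumed difference.

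**The case against.** The strongest defence is that the formal objectives agree with one another: the general aim and Aims 1 to 5 name metabolic indices and microbiota, with insulin resistance primary. The Abstract only says that supplementation may help, and the Discussion is conditional. On this view one loose sentence in the Background should be corrected and no endpoint added, especially since the estimate would be too imprecise to exclude zero in any scenario shown. Much of this stands. Rewording alone would cure the mismatch, and the fix offers it as a full alternative. The mismatch itself is not explained by the condensing of a journal article, because the aims are set out one by one and diabetes onset is not among them.

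A reader might go further and infer that the diabetes question cannot be answered at all. The article does not support that: fasting glucose and HbA1c run to month 18, so what is missing is a definition and a comparison, not the data.

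A reader might also infer that the plan, as written, removes everyone who converts. That is too strong as well. The Sample size and missing-data sections say the opposite of the Overview, and conversion seen only in the laboratory falls outside this rule. The text contradicts itself; it does not settle on removal.

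**Conclusion.** The point holds as a mismatch and a contradiction. Development of type 2 diabetes is a stated purpose without aim, outcome, analysis or sample size. The exclusion for medication change conflicts with full outcome collection and with intention-to-treat and, if applied, would lose likely converters selectively.

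The size of that selective loss cannot be given. Shrinking both arms equally would model attrition unrelated to outcome, whereas losing converters deletes events and lowers the observed risks. What can be sized is the precision of a diabetes comparison at full enrollment: 4–28% Fisher power for a halving and half-widths of about 11–18 points. That range rests wholly on the assumed 10–30% placebo risk, on a halving, and on all 40 per arm being at risk and followed up.

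The missing endpoint does not touch the choice of HOMA-IR as primary outcome. The plan should still be changed, because the repair is cheap and decides what the trial may conclude about prevention.

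**What to change.** 1. Reconcile the Overview, Sample size and Treatment of missing data sections so that a participant with a medication change remains in follow-up and in the intention-to-treat analysis. This concerns data collection and analysis only, not clinical management.

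2. Then choose one of two routes.
   - **Reword** the Abstract, Background and Discussion to match the general aim and Aims 1 to 5.
   - **Or add** onset of type 2 diabetes through month 18 as a secondary, estimation-only outcome:
     - Derive it from the scheduled fasting glucose and HbA1c, and from the glucose tolerance test only at visits where it is actually done, using the diagnostic criteria source already cited for entry.
     - Leave out of the risk set anyone whose baseline fasting glucose, 2-hour glucose or HbA1c is already in the diabetic range.
     - For analysis purposes, count start of glucose-lowering treatment for diabetes as an event.
     - Report risk differences with 95% CIs.

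3. On either route, draw no prevention claim from HOMA-IR or from a non-significant comparison.

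The cost is protocol wording, one extra table on the second route, continued follow-up that the Sample size section already promises, and a more modest claim. No added participants are needed.

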## The aims and hypotheses

### General aim

The general aim of the present investigation is to determine the effects of 6 months ingestion of probiotic or synbiotic on metabolic syndrome indices and gut microbiota composition through a triple-blind, randomized, placebo-controlled clinical trial in adults at risk of type 2 diabetes (prediabetes).

### The specific aims and hypotheses

#### Aim 1

To determine whether probiotic or synbiotic supplementation improves fasting plasma glucose, insulin resistance (primary outcome), and beta-cell function in individuals at elevated risk of developing T2DM. We hypothesize that probiotic and synbiotic supplementation will improve fasting plasma glucose, insulin sensitivity, and beta-cell function in these individuals compared with placebo.

#### Aim 2

To determine whether probiotic or synbiotic supplementation will improve lipid profiles in individuals at elevated risk of developing T2DM. We hypothesize that probiotic and synbiotic supplementation will reduce serum triglyceride and non-high-density lipoprotein (HDL) cholesterol, elevate HDL cholesterol, and improve low-density lipoprotein (LDL)/HDL, total cholesterol (TC)/HDL and triglyceride (TG)/HDL in these individuals.

#### Aim 3

To determine whether probiotic or synbiotic supplementation will improve anthropometric indicators in individuals at elevated risk of developing T2DM. We hypothesize that probiotic and synbiotic supplementation will improve body mass index (BMI), waist circumference and waist-to-hip ratio (WHR) in these individuals.

#### Aim 4

To determine the changes in abundance and ratio of two dominant groups of gut microbiota including Firmicutes and Bacteroidetes and their relation with metabolic syndrome indices during supplementation. We hypothesize that the change in Gram-positive gut microbiota (Firmicutes) and Firmicutes-to-Bacteroidetes ratio with probiotic and synbiotic supplementation will be correlated with the change observed in the metabolic variables.

#### Aim 5

To compare the effects of probiotic and synbiotic supplements on gut microbiota, anthropometric, glycemic, and lipid profiles. We hypothesize that synbiotic supplements will have more efficacy to improve these indicators than probiotic.

